#### Physical measures

The anthropometric assessment will be performed in the GP practice or outpatient clinic by a trained research assistant. Calibrated scales will be used to measure body weight to the nearest 0.5 kg, wearing light indoor clothing and no shoes. Height in cm will be measured to the nearest 0.1 cm on bare feet. Waist circumference will be measured twice with a tape to the nearest 0.1 cm at the level midway between the lowest rib margin and the iliac crest.

Systolic and diastolic blood pressure (in mmHg) will be measured in a seated position with a fully automated blood pressure monitor (OMRON M5-I). All measurements will be performed twice, mean values of the two measurements will be computed.

#### Laboratory tests

Fasting blood samples will be drawn at the laboratory to determine HbA1c, total cholesterol, LDL and HDL-cholesterol, triglycerides, glucose and insulin, to calculate HOMA [31].

#### Questionnaires

All participants will be asked to fill out a questionnaire (20 minutes), either at home via the internet or on paper. The questionnaire consists of cross-cultural validated questionnaires when possible.

#### Participant characteristics

At baseline, socio-demographic data (marital status, highest level of completed education, current employment), reasons to participate in the study, complete family history of diabetes in first and second degree relatives, illness and co-morbidity in the past, and use of medication will be assessed. Ethnicity will be assessed by asking own and parents' country of birth, duration of living in the Netherlands and self-reported ethnicity.

#### Body weight

Questions about body weight include: a) weight loss history (number of attempts to lose weight, received weight counselling by a GP, dietician or physiotherapist during the past 3 months, desired body weight and body weight history over the past five years), b) body weight perception (description of own body weight: answer categories include 'thin', 'average', 'somewhat overweight' and 'overweight') and c) Importance of body weight, assessed by a 5-point likert scale from very important to totally not important.

#### Lifestyle behaviours

Frequency and amount of fruit, vegetable and snack intake per week and nutrition habits will be assessed with a modified version of a frequently used food frequency questionnaire [32]. Moderate, vigorous physical activity and the amount of walking per week will be assessed with the IPAQ short form [33]. Smoking behaviour will be assessed by asking participants if they are a current smoker, an ex-smoker, or a never smoker. In case of a current smoker the number of cigarettes or other tobacco products will be assessed. Alcohol intake on weekdays and weekend days will be assessed separately.

#### Health status

Health outcome will be measured using the EQ5D questionnaire [34]. The Kessler-10 (K10) [35] will be used to assess level of psychological distress (e.g. anxiety and depressive symptoms). The Dutch version of the K10 is appropriate for screening depressive disorders in primary care [36]. In addition, life-events occurred in the past 6 months, and psychological treatment in the past will be assessed.

#### Determinants of health behaviour change

In the HAPA framework determinants of initial change have been identified: perceived risk, self-efficacy, outcome expectancies, leading to intentions and action planning.

Questions about *risk perception *will include perceived causal beliefs, consequences and control of diabetes, which were derived from the revised Illness Perception Questionnaire (IPQ-R) [37]. In addition, comparative risk (a lot lower to a lot higher), estimation of risk (very low to very high) and emotional representation (totally not worried to very worried) will be assessed with 7-point likert scales (questions derived from Claassen et al.[38]). Finally, participants will be asked to score whether they think that lowering the chance of diabetes is: 'very important to totally not important' and 'very easy to very difficult'.

*Self-efficacy *for healthy eating and physical activity is assessed by ten questions using a 4-point likert scale (very uncertain to very certain) [39].

*Outcome expectancies *for a healthy diet and increasing physical activity will be measured with 8 questions with a 5-point likert scale (totally disagree to totally agree) [40]

*Intention *and *action planning *to change health behaviours will be assessed on a 5-point likert scale ranging from totally disagree to totally agree, asking participants whether they plan to consciously eat healthier/exercise more/lose weight and if they have formulated a detailed action plan (what, when, how) for changing diet and physical activity [40].

### Process evaluation

To monitor program implementation a process evaluation will be carried out following a structured process evaluation plan [41]. Fidelity, reach, dose delivered and received of the intervention and materials will be assessed by means of a short questionnaire at the end of the second session. In addition, the health facilitators will be asked to evaluate the group sessions, directly after each session.

### Statistical analysis

Descriptive statistics will be applied to describe the study population at baseline. To determine the effect of the intervention on weight loss and to follow individual change over time we will use generalized linear mixed models and take into account different settings (e.g. intervention groups, trainers), clustering of family members and correlation between observations from same subject; i.e. using a three level structure. Potential confounders and effect modifiers (e.g. BMI at baseline, SES, gender and age) will be investigated. To test predictors of weight loss multiple regression analysis techniques will be performed. The level of significance is set at p < 0.05.

### Ethical approval

The study protocol, information letters and informed consent form were approved by the Medical Ethics Review Committee of the VU University Medical Center.

## Discussion

This randomised controlled trial is designed to evaluate the effectiveness of DiAlert in assisting overweight individuals with a family history of T2DM to lose weight in order to reduce their risk of developing T2DM. There is growing evidence for prevention of T2DM by lifestyle. However, an approach with a focus on family history combined with structured lifestyle education has not been utilized before. We assume that the DiAlert intervention will prove to be more effective than the control condition in achieving significant body weight loss at 3 months and 9 months. In addition, we expect to observe significant changes in metabolic, psychological and behavioural parameters following the intervention in both ethnic groups, resulting in reduced risk of developing T2DM.

The study has some limitations that should be mentioned. First, blinding of the participants will be impossible because they receive the intervention. To limit this bias, participants will not be informed about the outcomes of measurements, except when outcomes suggest diagnosis of diabetes based on guidelines. Furthermore, family history and overweight is not consistently recorded in patient registers of the GP in the Netherlands [42], which might hinder recruitment of participants. Therefore we will utilise different recruitment strategies. By recording the recruitment path of each participant, we will be able to take into account bias due to different motivations of participation in the study.

Despite the growing knowledge in the field of primary prevention, there is an urgent need for well-designed translational studies in populations at high-risk for diabetes. The challenge in offering an intervention in a primary care setting is to find the right balance between efficacy (intensity, follow-ups) and feasibility. Particularly, in the case of people who are just at risk for T2DM and not yet medically ill and not meeting with disadvantages and complications of the disease. To increase feasibility, the intervention will be delivered in close proximity to participants' homes, which could reduce barriers for participation. In addition, because DiAlert consists only of two interactive group sessions, we assume low drop-out rates. At last, delivery in GP practices or in the outpatient clinic could contribute to the perception of the reliability of the given information.

A group-based lifestyle education is a practical method for evidence-based prevention of T2DM in real-life settings [43]. However, the group composition is important to consider, particularly with respect to mix of socio-demographics, health profile (previous health warnings, overweight) and cultural background. By targeting at a population of Turkish origin we will be able to reach a broader population at risk for diabetes in the Netherlands. However, we should take cultural competence of materials and facilitators into account.

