## Methods/Design

### Study design

The DiAlert-study is a randomised controlled trial (RCT) testing the effectiveness of a lifestyle education programme in two groups: ethnic Dutch participants and participants of Turkish origin living in the Netherlands. We aim to include 134 Dutch and 134 Turkish overweight first degree relatives of T2DM patients. Measurements are scheduled at baseline, 3 and 9 months after the last group session (see Figure 1).

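### As written, only results suggesting diabetes may be disclosed to participants, although the trial also measures blood pressure, lipids and the K10

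*Protocol article*

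**What the plan says.** The rule on feedback of results stands in the limitations paragraph of the Discussion: "participants will not be informed about the outcomes of measurements, except when outcomes suggest diagnosis of diabetes based on guidelines". The reason comes just before it: "First, blinding of the participants will be impossible because they receive the intervention. To limit this bias". So the sentence is a general bar with one named exception, offered as a measure against bias.

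The measurement sections describe a wider set of clinical data:

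- Physical measures: "Systolic and diastolic blood pressure (in mmHg) will be measured in a seated position with a fully automated blood pressure monitor".
- Laboratory tests: "Fasting blood samples will be drawn at the laboratory to determine HbA1c, total cholesterol, LDL and HDL-cholesterol, triglycerides, glucose and insulin".
- Health status: the K10 is used to assess psychological distress, and the article adds that "The Dutch version of the K10 is appropriate for screening depressive disorders in primary care".

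On timing, Study design says: "Measurements are scheduled at baseline, 3 and 9 months after the last group session". The Background presents the programme as a way for overweight first-degree relatives to lower their risk of diabetes and associated cardiovascular disease. The Abstract describes Turkish immigrants as at high risk of both. Ethical approval records that a committee approved the protocol, information letters and consent form; none of these is shown.

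**The concern.** The authors accept that one kind of clinically important result overrides non-disclosure. They give no reason why others collected at the same visits do not. Staff who took the sentence at its word would have no basis for telling a participant about a clinically important blood pressure, lipid or K10 result.

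What is at stake is participant safety. The trial generates these results itself, in people chosen for raised risk. Study population excludes those with a diagnosed psychiatric disorder and those being treated for ischaemic heart disease, so some abnormal findings could be new to the participant. No estimate of the treatment effect is at stake.

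**Working it through.** The point rests on no figure in the plan, so the check is mainly a comparison of passages.

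**Step 1. Scope of the rule against what is measured.**

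| Measure | Where stated | Disclosure route in the article |
|---|---|---|
| Glucose, HbA1c | Laboratory tests | Yes, if the result suggests diabetes |
| Blood pressure | Physical measures | None |
| Total, LDL and HDL cholesterol, triglycerides | Laboratory tests | None |
| K10 | Health status | None |

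Of these four kinds of clinical measure, one falls under the exception. No other section of the article supplies a route for the remaining three.

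**Step 2. Is this silence or a statement?** An article may leave the handling of unexpected findings to the full protocol. Here it does not stay silent: it states a rule and names its one exception. There are two possibilities. If the approved documents hold a wider procedure, the published sentence describes it wrongly. If they do not, the sentence is the rule and the gap is real. The wording needs correction in either case.

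**Step 3. How long, and how many?** Visits fall at baseline and at 3 and 9 months after the last group session. The article says neither when results are released nor whether they ever are, so the period of non-disclosure is undefined. The rule reaches 4 × 67 = 268 planned participants. That is its scope, not a count of people affected. The article gives no expected frequency of abnormal results, so that count cannot be derived.

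**Step 4. What withholding does for bias.** Participants know their arm whether or not they see their results, so withholding cannot replace blinding. It can keep measurement feedback from acting as an intervention of its own. That second function does not require withholding clinically important results, provided one rule applies to both arms.

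**Step 5. Would a change touch the sample size?** The plan's inputs are a difference of 3.5%, an SD of 6%, 80% power and a significance level of 0.05 (taken as two-sided). The normal approximation gives n = 2 × (1.960 + 0.842)² / (3.5/6)² = 15.70 / 0.3403 = 46.1, so 47 per group. The two-sample t-test gives 47.1, so 48, close to the stated 50; power at 50 per group is 0.82. The inflation 50 / 0.75 = 66.7 gives the stated 67. The disclosure rule enters none of these terms, so changing it alters no sample size or power figure.

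**The case against.** The strongest reply is that this is one sentence in the limitations paragraph of a condensed article. It explains a bias precaution and is not presented as an incidental-findings procedure. An ethics committee approved documents that are not shown, and such procedures usually sit there. Measuring an outcome without feeding it back is also not in itself a contradiction. This stands in part. It rules out any claim that results were in fact withheld, but it does not rescue wording that admits only one exception.

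A second reply concerns the reason for the rule. Risk information is a core ingredient of DiAlert, and raising risk perception is a stated aim in Table 1. Returning personal blood pressure and lipid values could therefore act as an intervention in the leaflet arm. This stands, and it supports keeping routine withholding.

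A reader might infer more than the document supports in three places:

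- **That withholding does little against bias.** The article gives no figure, claims only to limit the bias, and says nothing about participants weighing themselves at home.
- **That findings would be hidden for up to 9 months.** That period is read off the visit schedule; it is not a stated disclosure period.
- **That the trial screens for depression and conceals the result.** The K10 is a self-completed measure of distress used as an outcome. The remark on screening supports the choice of instrument and does not describe a screening step in the trial.

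**Conclusion.** The point holds in a limited form. As written, the Discussion bars disclosure of every measurement outcome except one suggesting diabetes, while the trial also collects blood pressure, lipids and the K10. Followed literally, other clinically important results would not be passed on.

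This rests on two things: the sentence means what it says, and nothing else in the article widens it. The first is an assumption, because the operative documents are not available; the second was checked. The consequence is for participant safety and cannot be put into numbers. It is worth correcting because the correction is cheap and leaves the design intact. It is not evidence of a safety failure in the conduct of the trial.

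**What to change.** Reconcile the single-exception sentence in the Discussion with Physical measures, Laboratory tests and Health status, so that the exception is not limited to diabetes and also accounts for other clinically important findings. The investigators and the ethics committee should decide which findings count, at what levels and by what route; no level or referral rule is proposed here. If an approved procedure already exists, describe it or refer to it. The procedure should be identical in both arms, and each disclosure should be recorded by arm so that any imbalance is visible at analysis.

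All other results can still be withheld. The bias statement can stay if it is qualified to say that withholding limits measurement feedback and does not compensate for unblinded participants.

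The cost is a wording change and, if none exists, a notification procedure. The downside is that a few notified participants may change behaviour or medication, which could affect their later measurements. The rule is the same in both arms, and the record by arm shows how often this arises.

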### Future implementation

This short, but comprehensive intervention could contribute to the knowledge of prevention of T2DM in public health. If DiAlert proves to be effective in reduction of body weight, implementation will be considered. The process evaluation will provide us with barriers and facilitators that can be used to determine the optimal implementation strategy.
